### Study participants and recruitment

Pregnant women admitted in the delivery room of participating health facilities for delivery labour during the study recruitment period will be included in the study along with their new-borns. Eligible pregnant women are those for whom a vaginal delivery was considered as first option at admission and the monitoring of the childbirth labour was started. The study will have two components: (i) the direct observation of childbirth practices and (ii) data extraction from patient management tools to assess childbirth outcomes.
Direct observations of child birthing practices

The participants selection into the direct observation component of the study will follow the successive steps below:
ScreeningConsenting eligible participantsPre-inclusion of eligible participantsFinal inclusion of participants after initial examination

Pregnant women presenting in the delivery room will be systematically screened by the data collectors for basic eligibility criteria. Pregnant women that meet the following criteria will not be selected for the consent process:
Admission for a planned C-sectionManifest advanced stage of the laborMinors (age < 18 years)

The data collectors will then consent and pre-include the consenting participants in the study at this stage. After the initial examination will be excluded from the study:
Pregnant women for whom a decision of emergency reference is taken without administration of proper care

Eligible women at this stage are finally included in the study. Pre-inclusion data for women finally excluded will be discarded.
Data extraction to assess childbirth outcomes

The data extraction component of the study will include data from all pregnant women that were admitted in the study period and for whom the labor was monitored in the health facility. We will exclude:

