#### Secondary outcomes

The first secondary outcome is the level of adherence to EBPs by healthcare providers during childbirth and early postpartum. This will be measured as a rate of successful delivery of key EBPs included in the modified WHO-SCC at each birth event. The provision of key EBPs will be ascertained in a sample of birth events using direct observation with possible cross-validations with data from birth registries and mothers’ health books when necessary. The anticipated best practices to be assessed in this study include: the assessment for need of reference, the use of a partograph, assessment for history and actual bleeding, vision blurred, HIV status, correct use of magnesium sulfate, uterotonics and antibiotics, early initiation of breastfeeding and skin-to-skin contact, and discussions around family planning services.

The second secondary outcome is the rate of availability of essential safe childbirth supplies measured at health facility level. A facility assessment questionnaire will be used to collect data on the availability of essential safe childbirth supplies as baseline assessment prior to the onset of the study. Six months after the launch of the study an end line survey will be conducted using the same questionnaire.

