Two data collectors will be appointed permanently (day and night) in each regional hospital during the period of data collection to directly observe and document the healthcare providers’ practices. The observations for each birth event will take place at four critical junctures from admission to discharge: at the admission, before the woman starts pushing, soon after delivery and just before discharge from the hospital. The observation will be strictly passive with no interaction with the healthcare providers and the patients. However, the data collectors can alert the healthcare providers in the event of occurrence of a life-threatening complication. Furthermore, should healthcare providers not adhere to a standard putting mother-new-born pair at high risk (examples: no administration of ARTs, antibiotics, sulfate of magnesium when needed), the observer will intervene in a kindly manner to suggest that such practice may be worthwhile. The intervention of the observer will follow a suggestive process without any coercion on the healthcare provider being observed. In such a case it will be recommended to probe the healthcare provider questioning the relevance of such a practice. For example, what do you think of the administration of ARTs to this woman? Would that be relevant? The healthcare provider must not be driven to feel guilty or blamed for anything. Any suggestion deemed relevant will be made in an inconspicuous manner, meant to be a private communication between the observer and the relevant healthcare provider. If an EBP was adhered to only after a suggestion was made by the data collector, her/she will still record that particular EBP as not having been adhered to by the healthcare provider.

The observation will be conducted every day of the week and at any time without discontinuation until the target sample size is achieved. A data collector may observe only part of a birth event and the observation will be continued by another data collector. However, data on each critical juncture must be fully collected by the same data collector. Thus, once a data collector has initiated the observation for a given pause points, he/she can get off work only after having filled in all the items pertaining to that pause point.

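### The direct-observation sample drops women referred out without proper care and discards their data, so the adherence denominator depends on care given after randomisation and cannot be checked later

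*Protocol article*

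**What the plan says.** All places are in the Protocol article. Under Study participants and recruitment, women for direct observation pass through screening, consent, pre-inclusion and final inclusion. Enrolment is placed at admission, ahead of the initial examination. The text then states "After the initial examination will be excluded from the study" and names one group: "Pregnant women for whom a decision of emergency reference is taken without administration of proper care". It adds: "Pre-inclusion data for women finally excluded will be discarded".

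The outcome taken from this sample is adherence to essential best practices (EBPs), the first secondary outcome: "This will be measured as a rate of successful delivery of key EBPs included in the modified WHO-SCC at each birth event". The practices listed under Secondary outcomes include "the assessment for need of reference, the use of a partograph, assessment for history and actual bleeding, vision blurred, HIV status" and "correct use of magnesium sulfate, uterotonics and antibiotics". Under Direct observations, "The observations for each birth event will take place at four critical junctures from admission to discharge", and admission is the first of them.

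Three other statements bear on the point:
- Direct observations: a practice performed only after the observer's prompt stays in the data and is recorded as not adhered to.
- Study participants and recruitment: a woman who consents only after the initial examination has no data for the first pause point but contributes the later ones.
- Statistical methods: the analysis is by intention to treat.

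**The concern.** Among women with an emergency referral decision, the wording removes only those who did not receive proper care. Staying in the denominator therefore depends on what providers did at or just after the initial examination, which is part of what the adherence outcome measures. It also happens after the clusters have been randomised and after the checklist, training and supervision have begun to act on admission practice, so the intervention can change who is dropped. The two arms may then be compared on differently selected women, which does not sit well with a declared intention-to-treat analysis.

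Discarding the records makes this permanent. No later analysis plan can describe the excluded women, compare them by arm or run a sensitivity analysis. The plan handles the nearest comparable case the other way: a practice done only on prompting is kept and counted as a failure.

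**Working it through.** **Inputs.** From The adherence to EBPs (Sample size): control adherence 50%, effect 15 points (so 65% under intervention), type I error 5%, power 80%, 620 births per country. From Direct observations: 80 births per hospital. From the primary-outcome calculation, borrowed as an assumption: intra-class correlation 0.01. The two-sided test is also an assumption here. The share of women excluded is not given anywhere.

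**The plan's own figure.** Two proportions, 0.50 v 0.65, give 170 per arm. With 80 per hospital the design effect is 1 + 79 × 0.01 = 1.79, and 170 × 1.79 = 304.3, so 305 per arm and 610 in total. With 620/8 = 77.5 per hospital the design effect is 1.765 and the total is 602. Both are within 3% of 620, so the sample size is not in dispute.

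**Effect of the exclusion.** Let p be true adherence among all pre-included women, f the share excluded and a the adherence among those excluded. Observed adherence is (p − f·a)/(1 − f). For example, with a = 0: 0.50/0.96 = 52.1% and 0.65/0.98 = 66.3%, a contrast of 14.2 points; and 0.50/0.94 = 53.2% v 66.3% gives 13.1 points.

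Those contrasts give each excluded woman the weight of a whole birth. A woman who leaves after the initial examination could contribute at most the admission pause point. If the four pause points are weighted equally (an assumption) and each has adherence of 50% and 65%, only one quarter of the shift reaches the overall contrast: 15 + (14.2 − 15)/4 = 14.8 and 15 + (13.1 − 15)/4 = 14.5. The fifth column below is therefore also what the admission pause point alone would show. The last column is computed from unrounded contrasts.

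| Excluded, control / intervention (assumed) | a | Control | Intervention | Contrast, full weight | Contrast, one pause point of four |
|---|---|---|---|---|---|
| 2% / 2% | 0% | 51.0% | 66.3% | 15.3 | 15.1 |
| 4% / 2% | 0% | 52.1% | 66.3% | 14.2 | 14.8 |
| 5% / 2% | 0% | 52.6% | 66.3% | 13.7 | 14.7 |
| 6% / 2% | 0% | 53.2% | 66.3% | 13.1 | 14.5 |
| 10% / 5% | 0% | 55.6% | 68.4% | 12.9 | 14.5 |
| 2% / 5% | 0% | 51.0% | 68.4% | 17.4 | 15.6 |
| 5% / 2% | 100% | 47.4% | 64.3% | 16.9 | 15.5 |
| 10% / 5% | 100% | 44.4% | 63.2% | 18.7 | 15.9 |

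With no true effect (50% in both arms) and 5% / 2% excluded, the spurious contrast is 0.50/0.98 − 0.50/0.95 = −1.6 points if a = 0, and +1.6 points if a = 100%. One quarter of that is 0.4 points either way.

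The sign thus depends on which arm loses more women and on whether those lost were adherent. The documents settle neither.

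**The case against.** The strongest reply is that this is an ordinary eligibility rule. The same section limits the study to women whose labour monitoring was started, and the parallel exclusion for data extraction speaks of women referred on upon admission. On that reading the phrase means sent on at once, not badly treated. Such women have no birth event in the hospital, while adherence is defined per birth event. This reading is plausible, and the point does not need the harsher one. It does not remove the problem: inclusion still turns on whether care was given after the examination, and observations on a listed practice are still thrown away. The absence of a birth event would justify dropping every immediate referral, whereas the wording drops only those without proper care.

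A reader might infer more: that the rule deletes failures, flatters control adherence and shrinks the contrast. The documents do not support this. A woman with a referral decision has, on a plain reading, been assessed for need of reference, so a success may be lost as easily as a failure. The checklist could also prompt more early referral in the intervention arm, which would widen the contrast.

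A reader might also infer that admission data exist for all these women. They do not: consent may not delay care, and women who could not consent before the examination have no data for that pause point. Emergency referrals are plausibly among them.

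Two further objections stand. Study settings implies that onward referral from a regional hospital is uncommon. And adherence is a secondary outcome, although it is the first specific objective.

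**Conclusion.** The point holds as a matter of structure. Retention in the adherence denominator depends on care given after cluster randomisation, at a juncture that the checklist targets and the outcome scores, and the discard sentence makes the selection impossible to examine.

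Size and direction cannot be fixed from the documents. In every scenario shown above, the overall contrast moves by less than 1 point when an excluded woman counts for one of four equally weighted pause points; it falls by 0.2 points at 4% v 2% and by 0.5 points at 6% v 2%, with no adherence among those excluded. The shift would be about four times as large in a result reported for the admission pause point alone. All of this rests on assumed exclusion shares, equal weights and the plan's 50% and 65%. The case for change rests less on the likely size than on the fact that the bias would otherwise be unmeasurable.

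**What to change.** For the direct-observation component:

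- Remove the sentence that discards pre-inclusion data.
- Keep the admission pause-point data of every woman who consented before the initial examination, including those then referred out.
- Score the practices due before referral as done or not done, and treat later pause points as not applicable.
- Report the number of these referrals by arm, and show adherence with and without them.

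This changes measurement only and leaves the management of referral untouched. The cost is a change of wording, since the data are already being collected under consent. The downside is that a few women contribute one pause point only, so denominators differ by pause point. The plan already accepts this in mirror image for women who consent late. The observation sample would also be slightly wider at admission than the data-extraction sample, which keeps its own parallel exclusion; showing results both ways covers that difference.

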## Methods

### Trial design

The intervention will be delivered at health facility (cluster) level and outcomes measurements will be carried out at individual participant level. We will use a matched paired cluster randomized controlled trial design, where a pair of health facilities (one intervention and one control) are enrolled in the study at the same time. The study will be conducted in referral hospitals with gynaecologists and where surgical facilities for c-section and blood transfusion services are readily available. Eight (8) regional hospitals (4 intervention and 4 control sites) will be included in the study in each country, giving a total of 24 health facilities (12 in intervention and 12 in control arms) in the three countries. Within each matched pair of health facilities, one will be randomized to receive the intervention and one will receive the standard of care. Facilities will be matched using geographic location within the country, the size of the population covered by the health facility and the annual births volume of the facility. The study will combine two main components: a data extraction component (used to measure the incidence of poor childbirth outcomes) and a direct observation of childbirth practices (to assess the availability of safe childbirth supplies and the adherence of care providers to EBPs).

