All the women who were admitted in the child birthing room for elective caesarian section (before the labour has begun);All the women and their newborns that were transferred for additional care after a delivery outside of the participating health facility and those received for any other type of obstetric care not related to childbirth (abortions, miscarriages and antenatal care);Pregnant women referred to higher level of care upon admission without proper administration of care at the level of the participating health facility;Mother-newborn pairs for whom provider was prompted to adhere to best practices in order to prevent a life-threatening situation during the direct observation of childbirth practices.

The recruitment will be done by appointed data collectors in each health facility (direct observation) and the facility-based coaches (data extraction). The enrolment into the study for the direct observation of care practices will take place right at the admission in the health facility, before the initial examination is performed. The process of consenting participant will, however, not be caused to delay the health care and for participants that were not able to provide informed consent before initial examination we will not collect data for this pause-point. Data will be collected for the subsequent pause-points if we get informed consent from the women after initial examination. For the data extraction component of the study, the mother-newborn pairs will be consecutively recruited from 2 weeks after the launch of the intervention to 6 months or until the prespecified sample is reached for each health facility. For the direct observation of childbirth care practices, a sample of mother-new-born pairs will also be consecutively recruited among those admitted for childbirth labour in each health facility. This recruitment will start 2 months after the onset of the intervention in intervention facilities and will continue until the calculated sample size for each health facility is achieved.

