### Statistical methods

The analysis will be per intention to treat. Descriptive statistics for the study sample will be computed using means and standard deviations or medians and interquartile ranges (IQR) for continuous covariates, and proportions will be used to describe categorical variables. We will make use of the Rao-Scott chi-square test statistic, which adjusts for the matched-pair, cluster randomization scheme [24], to compare the rates of the primary and secondary outcomes in the comparison and intervention groups if the randomization scheme was found effective. Possible multivariable modeling techniques to correct for potential imbalances between study groups include Generalized estimating equations, multilevel Poisson modeling and multilevel cox models. The data analysis will be carried out using Stata 15.1 software. A *p*-value< 0.05 will be necessary to consider intervention and comparison groups significantly different.

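### Births in which an observer prompted the provider are dropped from the primary-outcome sample, an exclusion after allocation that depends on the care the checklist targets and contradicts intention to treat

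*Protocol article*

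**What the plan says.** Under Trial design, the primary outcome comes from "a data extraction component (used to measure the incidence of poor childbirth outcomes". Under Study participants and recruitment, that component starts broad: "The data extraction component of the study will include data from all pregnant women that were admitted in the study period", provided labour was monitored there. The list of exclusions that follows includes "Mother-newborn pairs for whom provider was prompted to adhere to best practices in order to prevent a life-threatening situation" during direct observation.

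The section Direct observations explains when this happens. Observers are otherwise passive but may make a suggestion "should healthcare providers not adhere to a standard putting mother-new-born pair at high risk". The same section says that a practice carried out only after such a suggestion is scored as not adhered to, so the birth stays in the adherence outcome.

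Under Study hypothesis and objectives, better adherence is the first specific objective. Under Statistical methods: "The analysis will be per intention to treat".

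**The concern.** The exclusion is not a baseline characteristic of the woman. It is decided during labour, after the hospital has been allocated and the checklist launched, and it is triggered by what the provider fails to do. If the checklist works, such failures are rarer in intervention hospitals, so control hospitals lose more births. The births lost are those judged to be at high risk. The arms then no longer contain comparable women, and the comparison is not by intention to treat.

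The protocol also treats the same births in two ways: a prompted birth counts in the adherence outcome and is deleted from the primary outcome.

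**Working it through.** **The plan's own figure.** Sample size section: 15% v 7.5%, two-sided 5%, 80% power, intra-class correlation 0.01, cluster size 300.
- Design effect = 1 + (300 − 1) × 0.01 = 3.99.
- The two-proportion formula with continuity correction gives 304 per group; 304 × 3.99 = 1213, against the stated 1200.
- Allowing for 5% non-response: 2400 / 0.95 = 2526, against the stated 2530.

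The sample size reproduces within rounding, so the point is not about that calculation.

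**Share of births exposed to the rule.** Direct observations plans 80 observed births per hospital; Data extraction plans 320. So f = 80 / 320 = 25%. This is a ceiling. Extraction starts 2 weeks after launch and may stop when its sample is full, while observation starts at 2 months. At the planning rate of two births a day, extraction runs from about day 14 to day 174 (320 / 2 = 160 days) and observation from about day 61 to day 101 (80 / 2 = 40 days), so they overlap fully. A hospital with about 7 eligible births a day (320 / 47 days = 6.8) would fill its extraction sample before observation begins.

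**Effect of dropping prompted births.** Let p be the event rate with all births kept (before any effect of the prompt), q the share of observed births prompted, and r the event risk in those births. The rate after exclusion is

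(p − f·q·r) / (1 − f·q).

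The documents give neither q nor r, so the values below are assumptions.

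| Prompted, control v intervention | r | Control rate | Intervention rate | Difference | Risk ratio |
|---|---|---|---|---|---|
| No exclusion | – | 15.0% | 7.5% | 7.5 points | 0.50 |
| 5% v 2% | 30% | 14.8% | 7.4% | 7.4 points | 0.50 |
| 10% v 3% | 60% | 13.8% | 7.1% | 6.7 points | 0.51 |
| 20% v 5% | 60% | 12.6% | 6.8% | 5.8 points | 0.54 |

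Middle row in full: control (0.15 − 0.025 × 0.6) / 0.975 = 0.1385; intervention (0.075 − 0.0075 × 0.6) / 0.9925 = 0.0710.

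Normal-approximation power (1200 per arm, design effect 3.99) is 83% without exclusion and 83%, 77% and 67% in the three scenarios. This ignores the small number of clusters, so only the change is informative.

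**Direction.** The absolute difference shrinks in all three scenarios. The ratio need not rise: with only a twofold gap in prompting it slips slightly in the checklist's favour (0.49 at 10% v 5% with r = 30%, and at 20% v 10% with r = 50%). Hence usually, not always, toward no effect.

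**Cost of keeping the births.** If prompts avert a fraction a of events in prompted births, keeping them gives a difference of 7.5 points − a·f·r·(q control − q intervention). For 10% v 3% and r = 60%, this is 7.5 − 1.05a points. It equals the 6.74 points left after exclusion when a = 0.76 / 1.05, about 72%. In the mildest scenario the break-even is about 34%.

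**The case against.** The strongest defence is that a prompted birth received care the study itself supplied, so its outcome reflects neither the checklist nor usual care. Dropping it is a reasonable attempt to remove contamination, and keeping it dilutes the contrast because prompts are expected more often in control hospitals. This stands in part: above the break-even values just shown, keeping the births attenuates more than excluding them. But exclusion deals with contamination by selecting on non-adherence, which breaks comparability of the arms. Leaving out the whole observation period in both arms deals with it without that selection.

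It is also fair that the size rests on assumptions. A 60% event risk is four times the 15% base rate, and one of the protocol's own examples of a prompt, omitted ARTs, matches no component of the composite. On the ratio scale the shift is small.

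Two stronger readings are tempting and not supported.
- A reader might infer that with no true effect the trial would appear to show harm. In the middle scenario the null rates become 13.8% v 14.7%, a gap of 0.8 points. The standard error is about 2.9 points (√(3.99 × 2 × 0.15 × 0.85 / 1200)), so the shift is under 0.3 standard errors.
- A reader might infer that the exclusion of "Pregnant women referred to higher level of care upon admission without proper administration of care at the level of the participating health facility" is an equal flaw biased toward benefit, because "the assessment for need of reference" is a measured practice. But eligibility already requires that labour monitoring was started, which most such women would not meet. The rule covers only referral without proper care, and a working checklist could bring more care before referral and so keep women in. Study settings also says that regional hospitals can manage most complications detected in time. With assumed referral of 2% to 5% differing by arm and event risk of 30% to 50%, the null ratio ranges from 0.92 to 1.09: direction unknown and size probably small.

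**Conclusion.** The point holds for the prompted-pair exclusion alone. It is applied after allocation to the primary-outcome sample, depends on provider behaviour that the intervention is designed to change, and cannot be squared with the stated intention-to-treat analysis. Nothing else in the article repairs it. That conclusion needs no assumed number.

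The size does. With at most a quarter of births exposed and the three scenarios above, the planned 7.5-point difference falls to between 7.4 and 5.8 points, usually a bias toward no effect. The loss ranges from negligible to material, and the documents cannot say which. The change is worth making because it is cheap and because births never extracted may be hard to recover later. The referral exclusion warrants no more than a count by arm.

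**What to change.** 1. Delete the prompted-pair exclusion from the primary analysis. Keep these births with the outcome that occurred, flag them in the extraction form, and report their number by arm.
2. Add a sensitivity analysis that excludes prompted pairs.
3. Add a second sensitivity analysis that omits all births admitted during each hospital's observation period, in both arms alike.
4. As a reporting note only, count by arm the women referred on admission and not included.

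The cost is a change of wording, one flag and one count, with no added participants; it should be made before extraction starts. The downside is that the kept births include care improved by the prompt, which dilutes the contrast and could attenuate more than exclusion if prompts avert most events in them. The second sensitivity analysis addresses this, with fewer births and so less precision. The observers' safety prompts are unchanged.
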